### 2.3 Trial Design & Flowchart

The study has been designed as a feasibility two-armed parallel group RCT with integrated process evaluation, as shown in the adapted CONSORT diagram in Figure 1. An RCT has been chosen because: (1) this is the gold standard design to determine causal associations, (2) a control group design is necessary because changes related to pregnancy and the postpartum period might impact outcomes (e.g. weight change) and make between group interactions less reliable than group*time interactions, and (3) the study will provide preliminary information on feasibility with regards to recruitment and retention, acceptability and outcome measures, before undertaking a large-scale RCT.

**Figure 1. CONSORT flowchart**

**29-32 weeks' gestation:** Dietician or researcher provide information to potentially eligible participant during group education session. Or clinician providing routine care to approach potentially eligible participants at first clinic appointment - brief verbal and written information given and verbal permission for researcher to contact sought

**Baseline / randomisation visit (29-33 weeks' gestation):** Eligibility confirmed; written informed consent (if not previously obtained); randomisation; demography; questionnaires; anthropometry; blood pressure; blood sample; OGTT, provided with 7 day accelerometer and instructions

**DECLINED or INELIGIBLE**

Routine demographic data recorded if agreed

**29-33 weeks' gestation:** Eligibility screening, responding to questions about the study and taking informed consent (researcher or clinician conducting routine appointment)

**Face-face MI session 5 (9 months postpartum)**

**Follow up data visit (9 months postpartum):** Questionnaires; anthropometry; blood pressure; blood sample; OGTT; provided with 7 day accelerometer

**Face-face MI session 4 (6 months postpartum)**

**Face-face MI session 3 (3 months postpartum)**

**DROP OUT**

Pre-collected data used if agreed

**Interim data visit (3 months postpartum):** Questionnaires; anthropometry; blood pressure; blood sample; OGTT; provided with 7 day accelerometer

**Face-face MI session 2 (33-37 weeks’ gestation)**

**CONTROL GROUP:**

Routine care

**INTERVENTION GROUP**

**Face-face MI session 1 (29-33 weeks’ gestation)**

**Given access to WhatsApp group, pedometer and website**

|  | Recruitment | Screening | Face-to-face session 1 | Face-to-face session 2 | Face-to-face session 3 | Face-to-face session 4 | Face-to-face session 5 | Interview |
| --- | --- | --- | --- | --- | --- | --- | --- | --- |
| Patient information | X |  |  |  |  |  |  |  |
| Inclusion and exclusion check | X |  |  |  |  |  |  |  |
| Patients who meet the study inclusion criteria | | | | | | | | |
| Informed consent |  | X |  |  |  |  |  |  |
| Demographics |  | X |  |  |  |  |  |  |
| Blood sample |  |  | X |  | X |  | X |  |
| Weight, height, waist circumference |  |  | X |  | X |  | X |  |
| Depression (PHQ 9) |  |  | X |  | X |  | X |  |
| Edinburgh Postnatal Depression Scale |  |  | X |  | X |  | X |  |
| Quality of life (EuroQol EQ-5D-5L) |  |  | X |  | X |  | X |  |
| Body Appreciation Scale |  |  | X |  | X |  | X |  |
| Three Factor Eating Questionnaire |  |  | X |  | X |  | X |  |
| Dietary Change Motivation Scale |  |  | X |  | X |  | X |  |
| **Risk Perception Survey for Developing Diabetes** |  |  | X |  | X |  | X |  |
| Multiple pass 24 hour diet recall (online) |  |  | X |  | X |  | X |  |
| Adapted GPAQ physical activity questionnaire |  |  | X |  | X |  | X |  |
| Sleep |  |  | X |  | X |  | X |  |
| Infant feeding intentions scale |  |  | X |  |  |  |  |  |
| Infant feeding |  |  |  |  | X |  | X |  |
| Infant data |  |  |  |  | X |  | X |  |
| Data from motion watch |  |  | X |  | X |  | X |  |
| What’sApp group and fitbit usage |  |  |  |  | X |  | X |  |
| Process evaluation |  |  |  |  |  |  |  | X |

**X = all participants**

**X = only participants randomised to intervention group**

**2.4 Outcome Measures**

The primary outcome is feasibility of the trial. This will be assessed during the process evaluation through:

- recruitment rate
- attrition rate
- reasons for non-acceptance
- trial procedures for randomisation
- amount of staff time required
- fidelity, measured through a self-report check-list
- staff feedback on feasibility
- participants’ satisfaction with the intervention
- acceptability of research procedures, data collection and overall experience of the trial

The secondary outcomes will assess preliminary efficacy of the intervention. We will measure the following :

- Oral Glucose Tolerance Test (OGTT) to assess differences ≥1 mmol/l in either fasting or two hour postprandial glucose
- Incident T2DM and a subsequent GDM pregnancy (NICE criteria)
- Relative and absolute weight loss at multiple time points considering the number of women achieving significant weight loss (>5%) at 3 and 9 months postpartum from a baseline of the booking appointment weight
- Lifestyle factors, following the Medical Research Council (2012) diet and physical activity measurement toolkit and from accelerometer
- Other metabolic and anthropometric factors will include HbA1c, waist circumference and blood pressure
- Psychological factors; depression/anxiety (PHQ9) and postnatal depression (Edinburgh postnatal depression scale)
- Health related quality of life- EuroQol EQ-5D-5L will be used to assess health related quality of life
- Diabetes risk perception (Risk Perception Survey for Developing Diabetes used in the DPP [9]).
- Infant factors- infant feeding intentions, breast feeding duration, weight gain and growth, and measure of attachment.
- Attitudes to body [23], eating behaviour [24] and motivation for dietary change [25].
- Additional data will include: age, ethnicity, deprivation, employment, education, pre-pregnancy BMI, parity, previous GDM and birth outcome data

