We have also adapted the activity and weight loss targets to reflect NICE guidance on weight loss and pregnancy (<https://www.nice.org.uk/guidance/ph27/chapter/1-recommendations#recommendation-3-supporting-women-after-childbirth>.). Our targets for physical activity during pregnancy have been modified to concord with the NICE guideline which states that: women who have not exercised routinely should begin with no more than 15 minutes of continuous exercise, three times per week, increasing gradually to daily 30-minute sessions. We have also amended the weight reduction target to state that weight loss should only be attempted at 6-8 weeks postpartum with the aim of ≥ 5% reduction by 12 months from that point. The pregnancy activity and dietary targets have also been informed by the findings of the UPBEAT study [21]. This study was undertaken by members of our team and targeted obese women in pregnancy and reported reduced gestational weight gain (GWG) and increased physical activity without any adverse events [22]. The intervention has been further adapted and designed following a structured format to facilitate adoption within current NHS care delivery systems. The target behavioral outcomes for each phase of the intervention are identified in table 1. These are the global targets, each woman will set their own individual goals.

| Table 1. Behavioural outcomes | | | |
| --- | --- | --- | --- |
| *Intervention Phase* | *Target behavioral outcomes* | | |
|  | *Physical Activity* | *Diet* | *Weight loss* |
| Pregnancy | 1. 15 minutes of moderate physical activity increasing to 30 minutes (brisk walking, swimming) 2. Walking increase by 20% aiming for 10,000 steps per day | 1. Increase: fruit and veg intake; whole grain foods. 2. Reduce snacks and sugary drinks, refined carbohydrates and portion sizes. 3. Eat breakfast. 4. No calorie targets will be set for pregnancy | Weight loss not applicable but relative GWG to be managed as per baseline BMI:  Baseline BMI 25-29, GWG ≤ 9kg; BMI ≥30, GWG ≤ 6kg*. |
| Early post-partum (0-3 months) | 1. 30 Minutes of moderate physical activity 3 times per week increasing to daily. 2. Walking 10,000 steps per day | 1-3 as per pregnancy +   1. Breast feeding 2. Daily calorie target = 1,200 (+330 if breast feeding). | 1-2KG weight loss per week from 2 months post-partum. |

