| Up to first year of life | 1-2 as per early post-partum | 1-3 as per pregnancy +   1. Daily calorie target = 1,200 (+400 if breast feeding). | ≥5% weight loss from 2 months post-partum. |
| *= Cedergren, M. (2007) Optimal gestational weight gain for body mass index categories. Obstet Gynecol. 2007 Oct;110(4):759-64. | | | |

The intervention is comprised of 5 face to face interactions (60 minutes) across the antenatal and postpartum periods delivered using motivational interviewing (MI) techniques. The focus of the sessions are targeted to reflect the changing context of needs during pregnancy and the postpartum period. The intervention is supported by a facilitated ‘WhatsApp’ group, motivational text messages, a pedometer and a website. An overview of the GODDESS intervention is provided in figure 1.

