### 3. Sample Size, Selection and Withdrawal of Subjects

A convenience sample of 60 women with current GDM, 30 in each arm will be recruited. King’s College Hospital antenatal diabetes clinic sees around 200 new patients with GDM a year, equating to 17 a month, and Guy’s and St Thomas’ Hospitals see 700 (58 a month). Participants will be recruited opportunistically at their routine clinic appointment upon diagnosis of GDM, group education session the following week, or at a following clinic visit, by a diabetes nurse, consultant or dietician. We estimate that with a 30% recruitment rate we can recruit our sample within 3 months, or with a 15% recruitment rate we can recruit within 6 months. The intervention will last approximately 12 months (depending on gestational stage at diagnosis – usually this is around 28 weeks but can be earlier), with follow-up stopping at 9 months postpartum. We aim to start recruitment, ethical approval permitting, in March 2018, and finish data collection in September 2019. We expect the data to be analysed by December 2019.

Pregnant women have been chosen because: (1) previous research and our qualitative research indicates this is the best time to recruit women to start providing support, (2) women are already engaged with health services so may be easier to recruit, (3) women may be more receptive to behaviour change support during pregnancy, and (4) the highest cumulative incidence of T2DM after GDM is in the first 5 years postpartum, so any intervention should start as soon as possible after identification of GDM.

Potential participants will be identified by the clinical team working at KCH and GSTT. Potential participants will be given the participant information sheet explaining the purpose of the study. Participants who indicate a potential interest in the study will be given the opportunity to consider their participation in the study before being scanned by the researcher for full eligibility using the eligibility screening form. After screening, if the patient is eligible they will undergo consenting, either on the same day or another day at their convenience. Participants may withdraw their interest in the study at any point during the screening and consenting process and their details will not be stored.

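### The >5% weight-loss count from booking weight does not measure the intervention's own ≥5% postpartum target, and the statements of that target need reconciling

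*Protocol*

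**What the plan says.** **Outcome.** Among the secondary outcomes, protocol section 2.4 (Outcome Measures) lists relative and absolute weight loss at several times, including the number of women with "significant weight loss (>5%) at 3 and 9 months postpartum from a baseline of the booking appointment weight".

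**Target, in the text.** Section 2.2 says that "weight loss should only be attempted at 6-8 weeks postpartum with the aim of ≥ 5% reduction by 12 months from that point".

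**Target, in Table 1 (behavioural outcomes).** The row for 0-3 months postpartum gives "1-2KG weight loss per week from 2 months post-partum" and, in its diet column, "Daily calorie target = 1,200 (+330 if breast feeding". The row for the infant's first year gives "≥5% weight loss from 2 months post-partum". The text introduces these as global targets and adds that each woman sets her own goals.

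**Measurement.** The schedule table in section 2.3 and the visit lists in section 4.2 place study weights at session 1 (29-33 weeks' gestation), 3 months and 9 months postpartum. The first postpartum data visit is the "Interim data visit (3 months postpartum): Questionnaires; anthropometry; blood pressure; blood sample; OGTT; provided with 7 day accelerometer". Section 4.2 takes booking BMI from the patient record. Section 3 describes the trial "with follow-up stopping at 9 months postpartum".

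**The concern.** The outcome and the target look like the same 5%, but they differ in three ways: the reference weight (booking against 6-8 weeks or 2 months postpartum), the date (3 and 9 months against about 12 to 14 months postpartum) and the threshold (>5% against ≥5%). Someone reading the final count could take it as the share of women who met the intervention's target, which it is not. The target's own reference weight is not scheduled to be measured, and its end date falls after follow-up stops.

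The statements of the target also do not agree with one another. The text restricts attempted weight loss to 6-8 weeks postpartum onward. Table 1 sets a daily calorie target for the whole 0-3 month phase and gives it no later start. This part bears on participant safety as well as on interpretation.

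**Working it through.** There is no sample-size or power figure to reproduce here. The check is of dates and of the relation between the two reference weights.

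**1. Dates.** One month is 365.25/12/7 = 4.348 weeks, so 6 weeks is 1.38 months and 8 weeks is 1.84 months. For a 12-month period from the start (text of section 2.2):

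| Start | End, months postpartum | 9-month visit: elapsed | Share of 12 months | Short by | Weeks elapsed at 3-month visit |
|---|---|---|---|---|---|
| 6 weeks | 1.38 + 12 = 13.4 | 9 − 1.38 = 7.6 months | 64% | 4.4 months | 7.0 |
| 8 weeks | 1.84 + 12 = 13.8 | 9 − 1.84 = 7.2 months | 60% | 4.8 months | 5.0 |
| 2 months | 2 + 12 = 14.0 | 9 − 2 = 7.0 months | 58% | 5.0 months | 4.3 |

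If Table 1's first-year row means 12 months postpartum, the period from 2 months is 10 months. The 9-month visit is then 7/10 = 70% of the way through and 12 − 9 = 3 months short. On every reading the target date is 3 to 5 months after the last visit, and the 3-month count covers about 4 to 7 weeks of attempted loss.

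**2. Reference weight.** Let the 2-month weight be (1 + r) times booking weight. The documents give no value for r, so a range is assumed.
- A 5% loss from 2 months leaves the woman at 0.95(1 + r) − 1 relative to booking.
- To be 5% below booking she must lose 1 − 0.95/(1 + r) of her 2-month weight.

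| Assumed r | After a 5% loss, relative to booking | Loss from 2 months needed for 5% below booking |
|---|---|---|
| −6% | −10.7% | none (already more than 5% below) |
| 0% | −5.0% | 5.0% |
| +2.5% | −2.6% | 7.3% |
| +5% | −0.25% | 9.5% |
| +10% | +4.5% | 13.6% |

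Example at r = +5%, with 80 kg at booking and 84 kg at 2 months (both assumed): 84 × 0.95 = 79.8 kg, and (79.8 − 80)/80 = −0.25%, so she meets the target but is not counted. To reach 76 kg (5% below booking) she must lose (84 − 76)/84 = 9.5%. At r = −6% the error reverses: a woman who simply holds her 2-month weight is counted. At r = 0% the criteria nearly coincide and differ only for a loss of exactly 5%.

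**3. Can the 3-month weight stand in for the missing reference?** No. It is taken after loss has begun. At Table 1's own 1-2 kg per week from 2 months, 4.3 to 8.7 kg would have gone by 3 months, which is 5% to 10% of an assumed 84 kg.

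**4. The target statements side by side.**
- *Start of attempted loss:* 6-8 weeks in the text, 2 months (8.7 weeks) in Table 1.
- *Start of the calorie target:* undated within the 0-3 month row, although the weight column of the same row is dated.
- *End of the ≥5% period:* 12 months after the start in the text, the infant's first year in Table 1.

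**The case against.** The strongest reply is that a coaching target and an efficacy outcome need not be the same thing. The protocol never says that the >5% count measures attainment of the target, and each woman sets her own goals. Booking weight is also the better reference for comparing arms. It precedes randomisation, and the intervention begins in pregnancy with aims for gestational weight gain. A 2-month weight would be measured after randomisation and could remove part of any effect. A continuous analysis is already within the text: section 2.4 lists relative and absolute loss, and its statistics part treats weight loss as a continuous variable. All of this stands. It is why booking weight should stay, and why the fault lies in how the count will be read and not in the comparison between arms.

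Four stronger readings are tempting and are not supported.
- A reader might infer that women who meet their target are scored as failures, so that the effect is understated. That depends on r, which the documents do not give, and it reverses when r is low enough.
- A reader might infer that a misleading responder rate feeds the definitive trial. The statistics part of section 2.4 carries forward an effect size and a standard deviation.
- A reader might infer that fidelity cannot be judged. Section 2.4 measures fidelity by a self-report checklist, and nothing says that it is scored in kilograms or calories.
- A reader might infer that 1-2 kg per week contradicts ≥5%. Spread over 52 weeks, 5% of an assumed 70-100 kg is 0.07-0.10 kg per week, some 10 to 30 times slower. But the protocol never spreads it evenly: one entry is a rate in an early phase, the other a cumulative minimum. How they relate needs explaining, but they are not strictly contradictory.

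**Conclusion.** The point holds in limited form. The >5% count at 3 and 9 months is not a measure of the intervention's weight target. The target's reference weight is unscheduled, its end date is 3 to 5 months beyond the last visit, the 3-month count reflects only about 4 to 7 weeks of attempted loss, and the thresholds differ. The dates follow from the protocol alone. The extent and direction of misclassification rest on the assumed range of r and cannot be fixed from the documents. The comparison between arms from booking weight remains valid.

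Separately, the text and Table 1 of section 2.2 disagree on when weight loss starts and when the ≥5% period ends, and the calorie target for 0-3 months has no start date compatible with the text. Severity is minor to moderate, since weight is a secondary outcome of a feasibility trial. The calorie-target discrepancy is the part to settle before recruitment.

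**What to change.** **Outcome.** Keep booking weight as the reference. Make the 9-month weight difference from booking, continuous and adjusted for booking weight, the main weight analysis. Report the >5% counts at 3 and 9 months as descriptive, and state in section 2.4 that they are not attainment of the section 2.2 target. Either align the ≥5% and >5% thresholds or state that they differ on purpose. If target attainment is also wanted, a 6-8 week weight could be abstracted where routine records hold one. The protocol does not show that they do, and 9 months should then be labelled an interim point.

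**Intervention wording.** The investigator should reconcile the text and Table 1 of section 2.2 on the start of attempted weight loss, the start of the daily calorie target and the end date of the ≥5% target, and should say how the 1-2 kg per week entry relates to the ≥5% target. No clinical value is proposed here.

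**Cost.** Protocol wording, and at most one extra weight abstracted per woman. The booking measure is already to be taken from the record.

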**3.2 Exclusion Criteria**

- Unable to consent
- Under 18 years
- BMI <24, or <22 in Asian ethnic groups
- ≥31 weeks pregnant
- Unable to speak and understand English
- Serious mental illness
- No access to the internet

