| Content:   - Reflect on birth experience and on early postpartum goals, affirming what they have achieved and learning reflectively from their experiences, attending to self-efficacy defects and directing to ongoing goals. - Elicit what the patient thinks will be important going forward to sustain and adapt their lifestyle as the infant grows and their needs change- e.g. weaning and changing socialisation. - Elicit what social and wider resources can help them. - Elicit ways in which the wider family might develop an enhanced lifestyle. - Share ideas on prevention activities from the 3-6 month period using prompt cards- reflect on infant and family health context. - Set SMART goals with patient on prevention activities for first 3-6 month postpartum period. Goals can either be specific lifestyle goals or if patient is not yet ready for action they can be reflective exercises designed to enhance motivation. - Review goal attainment data and pedometer use and explore with patient strategies to increase steps- set a new target. - Discuss patients weight with them in a positive way and any relevant blood tests. - Explain follow-up support to be provided.   Materials:   - Prompt cards with ideas for healthy eating (smart eating), activity ideas (introducing FITT principles); infant and family nutrition; and strategies for being active with a young infant.   Targets:   - Patient remains motivated and activated. - Patient sets goals for 3-6 month period. - Patient is using the pedometer and WhatsApp group. |
| **Session 4: 6 months postpartum (60 minutes)** |

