**5.2 Sample Collection/Labelling/Logging**

Blood samples will be tracked and identifiable by the unique patient code. Sample results will be entered onto the patient record.

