### 6. Assessment of Safety

We have carefully considered the potential clinical hazards associated with this study. These have been discussed by clinical colleagues not directly involved in the study. There are no major risks involved with participation in this study. The study will have in place the following safety monitoring procedures: an incident log for every patient to record any adverse events; an incident log for all clinical research areas to monitor adherence to study protocol and SOP and for recording any incidents that may occur in the conduct of the study; weekly team meetings to consider any difficulties or potential hazards; and clear line of reporting for any adverse events. All team members have completed the KHP Good Clinical Practice. The clinical team will be advised of the patient’s participation in the study to ensure no contradicting intervention during the study.

The responsibility for the conduct of the study resides with all team members with overall responsibility resting with the Chief Investigator (CI). In addition to the weekly team meetings a monthly trial monitoring committee will be held for the duration of the study. This committee is comprised of: the CI, motivational interviewer, 1 diabetes consultant psychiatrist, 1 diabetes medical consultant, 1 diabetes nurse consultant, 2 researchers, a patient representative and a representative from the CTU.

Ethical issues around provision of information to the usual care group will be addressed by providing patients in this group with information about diabetes and healthy lifestyles after completion of follow-up measurements.

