**9.3 Record Retention and Archiving**

The Chief Investigator (CI) and the research team will have access to participants' personal data during the study. Participants will be informed, both verbally and through a Patient Information Sheet, that the CI and the research team will access their medical records during the study, in order to record their clinical information. Participants will sign an Informed Consent to confirm their willingness for the research team to access their personal information*.*

Data files will be stored on a password protected computer at the researcher’s University. Paper questionnaires will be stored in a locked filing cabinet in a research office at King's College London (KCL). This data will be primarily analysed by the PhD student with discussion of the analysis with academic supervisors and members of the research team throughout. Support from a statistician will be sought in case of need. Data analysis will be carried out in KCL, using SPSS on a password protected university computer.

Each participant will be assigned a unique study identifier and all data will be coded with that study identifier. Personalised information with the unique study identifier will be managed securely in restricted access, lockable containers at King’s College London (KCL).

No personalised data will be stored electronically, all data will be anonymised and any electronic data will be stored on a password protected university computers. The data held on these computers will not be identifiable back to personalised data.

Following completion of the study the personal data will be stored locally and accessed for 6-12 months after the study has ended. The electronic data generated by the study will be stored electronically on a university computer at King’s College London for 5 years. It will not contain any participant identifiable data and will only be used if there are any queries regarding the study after publication and future study design.

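### Depression is scored on two scales at three visits, but the protocol names nobody to read the scores and does not link them to its own safety process

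*Protocol*

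**What the plan says.** Section 2.4 (Outcome Measures) places the two scales among the measures of preliminary efficacy: "Psychological factors; depression/anxiety (PHQ9) and postnatal depression (Edinburgh postnatal depression scale". The assessment schedule in section 2.3 marks three occasions for the first ("Depression (PHQ 9) | | | X | | X | | X") and the same three for the Edinburgh scale. Section 4.2 lists both at data collection visits 1, 2 and 3.

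On where results go, section 5.2 says of blood tests: "Sample results will be entered onto the patient record". Section 4.4 has the interviewer take up weight and blood results with the woman; for session 3 it reads "Discuss patients weight with them in a positive way and any relevant blood tests". On questionnaires, section 9.3 says "Paper questionnaires will be stored in a locked filing cabinet in a research office". It adds that data held on the computers cannot be traced back to personal details, and on analysis it says "This data will be primarily analysed by the PhD student with discussion of the analysis with academic supervisors".

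On safety, section 6 provides "an incident log for every patient to record any adverse events", weekly team meetings on difficulties and hazards, and a monthly committee that includes a consultant psychiatrist. Section 9.2 gives the case report form a patient-safety purpose. Its list of questionnaires names the Hospital Anxiety and Depression Scale and neither PHQ9 nor the Edinburgh scale. Section 3.2 excludes women with "Serious mental illness", without defining the term or tying it to a score.

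**The concern.** The protocol treats mental health as relevant to safety: it excludes on that ground and seats a psychiatrist on the monitoring committee. It then collects repeated depression scores in pregnancy and after birth and handles them, as far as the text goes, as research data. A safety log or weekly meeting can only consider what someone has brought to it, and an unscored form brings nothing. At stake are the women themselves, in both arms, and the section 6 statement that participation carries no major risks. For mood, that statement could not be checked during the trial.

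There is also a question of bias. Participants know their allocation (section 4.3), and the planned efficacy analysis uses group-by-time interactions, which rest on the baseline value. Self-reported mood recorded after a woman learns her arm is not a clean baseline.

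**Working it through.** The protocol states no figure on this point to reproduce. The check is a count and a comparison of sections.

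**Count of assessments.** Scales: 2 (section 2.4). Occasions: 3 (sections 2.3 and 4.2). Women: 60 (section 3).
- Per woman: 2 × 3 = 6 forms.
- Whole trial, before attrition: 6 × 60 = 360 forms.

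The schedule's legend separates marks for all participants from marks for the intervention arm, but that distinction does not show in the text I worked from. I take both arms from section 4.2, which lists the scales at every data visit without naming an arm.

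**Where each kind of result goes.**

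| Result | Stated destination | Stated use during the trial |
|---|---|---|
| Blood tests | Patient record (5.2) | Discussed in sessions 3 to 5 (4.4) |
| Weight | Case report form (9.2) | Discussed in sessions 3 to 5 (4.4) |
| PHQ9, Edinburgh scale | Paper in a research cabinet; electronic data coded (9.3) | None stated |

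**Does any provision oblige someone to read or act on a score?**
- Section 3.2, exclusion: no link to either scale.
- Section 3.3, withdrawal: applies to a woman who is unwell and cannot comply, not to a score.
- Section 6, log, meetings and committee: general in scope, no mention of scores.
- Section 9.2, case report form: a general safety purpose, no reader or time given, and neither scheduled scale listed.
- Appendix 1: serious adverse event reporting, no mention of scores.

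Provisions found: 0.

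**Which mood scales?** Sections 2.3, 2.4 and 4.2 agree on PHQ9 and the Edinburgh scale. Section 9.2 names another. They cannot all describe the same data collection.

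**Order at baseline.** The flowchart box for the baseline visit in section 2.3 lists eligibility, consent, randomisation, demography, then questionnaires. The schedule places the baseline scales in the column for the first face-to-face session, which is itself part of the intervention. Section 4.2 does not say whether visit 1 comes before or after randomisation. A list need not be a time order, but no section puts the scales first.

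**How long could a form wait?** This assumes that nobody looks before the analysis. Recruitment in March 2018 at about 30 weeks, plus about 10 weeks to birth, plus 3 months gives a 3-month visit around August 2018. Section 3 ends data collection in September 2019 and expects analysis by December 2019. August 2018 to September 2019 is 13 months, and to December 2019 it is 16 months. Forms collected near the end of the trial would wait far less.

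**The case against.** The strongest reply is that this is silence, not error. Section 5.2 says blood results enter the record; no section says that other results do not. A reader might infer that depression scores go to the research analysis and nowhere else, but the protocol never says so. That part of the reply stands.

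Safeguards also exist. The case report form has a safety purpose, the team meets weekly, the committee has a psychiatrist and includes the motivational interviewer, and the clinical team knows who is taking part. Section 9.1 keeps tracking records that tie study number to person, so coding would not stop staff from acting on a score. Section 6 mentions operating procedures and section 9.5 a monitoring plan, and either might cover score handling. All this shows that a high score could be noticed. It does not show that anyone must look: no procedure is cited for this purpose, and control women have no sessions in which low mood might come up. Reading scores for safety is trial conduct, so it is not a matter normally left to an analysis plan.

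A reader might also infer that a baseline score cannot inform the mental-illness exclusion. That goes too far. The flowchart confirms eligibility again at the baseline visit, and the protocol does not say the exclusion was meant to rest on a score.

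**Conclusion.** The point holds in this form: safety-relevant scores are collected from all women at three visits, and the protocol does not connect them to the safety process it already has. The conflict over which mood scales are used, and the listing of randomisation before the baseline questionnaires, are on the face of the text. The change should be made; it does not call the trial's feasibility aims into question.

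The protocol does not support a size in women. If 10-20% were assumed to score in a clinically relevant range at some visit, that would be 0.10 × 60 = 6 to 0.20 × 60 = 12 women, but the rate is an assumption and does not describe severe depression. A reader might infer that severely depressed women will complete the programme unnoticed. The text shows only that nothing prevents it. The 13 to 16 months is likewise the wait for an early recruit's 3-month form if no one looks before analysis, not an expected delay; section 9.3 in fact describes discussion of the analysis throughout.

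The conclusion assumes that no separate procedure governs these scores. If one does, the remedy reduces to citing it and settling the scales and the baseline order.

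**What to change.** - Reconcile sections 2.3, 2.4, 4.2 and 9.2 on which mood scales are used, so that the case report form matches the schedule.
- In section 4.2, state that existing staff score the forms by study number at each data visit, in both arms, and name the role responsible. State that scores feed into the section 6 process (incident log, weekly meeting, committee). The threshold, the timing of any escalation and the clinical response are for the investigators and the committee psychiatrist to set.
- State in sections 2.3 and 4.2 that the baseline scales are completed before randomisation.
- Leave to the investigators whether scores bear on the mental-illness exclusion, and record the decision in section 3.2.

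The cost is protocol and information-sheet wording and some minutes of scoring per visit. Care prompted by a score could alter later mood scores. It should not be assumed to do so equally by arm: if the intervention affects mood, the number of scores passed on could differ between arms. Recording each score passed on, by arm, lets this be reported beside the mood outcomes.
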